### Sample storage

Where sufficient budget is available, sputum samples with at least 0.5 ml of residual specimen and urine with at least 0.2 ml residual specimen will be eligible for storage for 5 years and, if appropriate, tested locally. Venous blood as serum or plasma may also be stored when sufficient volume remains. All samples will be stored in deep freezers (−80°C) until testing. Methods for sample preservation will follow standard operating procedures developed in consultation with FIND for sample storage. Anonymised CXRs will be stored on the Box server and potentially used for product development and evaluation.

### The establishment of a paediatric training CXR library

Anonymised CXRs from children and young adolescents will be annotated and reviewed by WWR and matched with MRS and TB definition categorisation to establish a library of images that can be used for CAD software development. The library will be made available to software developers, subject to global access terms.

### Study outcomes and endpoints

In this 4-year project, the Start4All team will work towards three portfolio-level outcomes, which focus on: 1) Accelerating the introduction and adoption of existing TB diagnostic tools and novel TB test combination packages at primary health care level and outreach approaches to increase access to timely detection and linkage to care in LMICs; 2) Developing the conditions for sustainable and equitable access to TB diagnostics tools and TB test combination packages integrated within primary health care; and 3) Strengthening global alliances and national partnerships to enable scale-up. This protocol will work towards outcome 1 with the following study endpoints:

### Primary study endpoint

Generation of robust estimates of the diagnostic accuracy and performance of TB tests and TB test combinations in primary health care settings and key vulnerable populations (KVPs).

### Secondary study endpoints

Estimates of the predicted performance of TB test combinations and how they perform in specific populations.Selection of the optimal TB test combinations for implementation and scale-up in primary health care settings and KVPs based on their feasibility, acceptability, and modelled accuracy and cost-efficiency.

### Study vigilance

Study vigilance procedures define adverse events (AEs) as any unfavourable clinical or biological occurrence during study participation, regardless of causality, and serious adverse events (SAEs) according to International Council for Harmonisation criteria (e.g., death, life-threatening events, hospitalisation, disability, congenital anomaly, or other medically important events). Severity will be graded using the Division of AIDS toxicity table,^21^ and investigators will assess causality in relation to study procedures and concomitant treatments. Given the low-risk, non-interventional nature of this diagnostic study, only limited AEs are expected and routine AE reporting will be restricted to events associated with gastric aspiration in children only. SAE reporting will be limited to deaths and life-threatening events, which must be reported promptly to the sponsor and relevant authorities.

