### Study participants

Adults will be recruited from lowest level health care facilities (primary health care and district hospitals) across all countries and CBCF in Bangladesh, Cameroon, Nigeria, and Viet Nam. Adults are categorised as 15 years of age and above in Bangladesh, Cameroon, Kenya, Nigeria, and Viet Nam and 18 years of age and above in Brazil and Malawi. Children will be recruited from health care facilities (primary health care and district hospitals) from Cameroon and Viet Nam. Children are categorised as 1–14 years inclusive.

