### Participant flow

For individuals recruited via community-based screening, a CXR will be taken prior to study enrolment, supported by the national NTP as routine practice in CBCF activities. For those recruited via facility-based screening, CXR will occur after study enrolment. Individuals who meet the eligibility criteria will then be invited to a private room within the health care facility, provided with a patient information leaflet, and given an opportunity to ask any questions about participation. They will be ensured their decision to agree or decline the invitation will not negatively impact their routine care. Following written informed consent, individuals will be interviewed by the Start4All study team and a comprehensive case report form (CRF) will be taken (Supplementary Material 3). This will include key demographics, TB history – both personal and household – and data on associated TB risk factors. Participants will then be asked to provide two spot sputum samples 30 minutes apart, whole blood, a CXR (for those enrolled via FBCF), and urine. The Figure outlines the specimen collection procedure and testing conducted as part of the study. For children, where sufficient sputum samples cannot be obtained, per national guidelines, one or more of the following specimens will be taken to allow reference standard testing: induced sputum, gastric aspirate, nasopharyngeal aspirate, and stool. In Cameroon, venous whole blood will be used as this is routine clinical practice, but for all other countries capillary whole blood will be used from a single finger prick sample. For all adults, only one PA CXR will be taken. Thus, for individuals recruited through CBCF, the CXR taken during pre-consent eligibility screening will be used for CAD software processing, while those recruited through FBCF, will have their CXR taken and processed with the CAD software following study enrolment. For children aged <10, an additional lateral CXR image will be taken.

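### Events after induced sputum or nasopharyngeal aspiration in children that are neither fatal nor life-threatening enter neither of the two safety reporting channels the protocol describes

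*Protocol article*

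**What the plan says.** The Study vigilance section begins with wide definitions. An adverse event is "any unfavourable clinical or biological occurrence during study participation, regardless of causality". Serious events follow the ICH criteria, illustrated as "death, life-threatening events, hospitalisation, disability, congenital anomaly, or other medically important events". Investigators grade severity and judge causality against study procedures and concomitant treatments.

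The section then narrows what is reported, because the study is non-interventional and carries little risk. There are two channels:

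- Routine: "routine AE reporting will be restricted to events associated with gastric aspiration in children only".
- Serious: "SAE reporting will be limited to deaths and life-threatening events, which must be reported promptly to the sponsor and relevant authorities".

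The Participant flow section covers children from whom enough sputum cannot be obtained. Referring to national guidelines, it says that "one or more of the following specimens will be taken to allow reference standard testing" and names "induced sputum, gastric aspirate, nasopharyngeal aspirate, and stool". The Study participants section places these children in two countries: "Children will be recruited from health care facilities (primary health care and district hospitals) from Cameroon and Viet Nam". They are aged 1 to 14 years.

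**The concern.** Participant flow gives three aspiration or induction procedures the same purpose, in one list, under one reference to national guidelines. Study vigilance opens the routine channel to one of the three. The serious channel does not make up the difference, because it stops at death and threat to life, while the section's own definition of a serious event goes further and includes hospitalisation.

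What is at stake is oversight of child participants. If a child is admitted after sputum induction and the investigator judges the admission related to the procedure, the event is serious by the protocol's definition, yet no rule in the article sends it to the sponsor or the authorities. The same admission after gastric aspiration would at least reach the routine channel. Accuracy estimates, sample size and analysis are unaffected.

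**Working it through.** No formula applies and there is no figure to reproduce. The check sets the specimen list in Participant flow against the two channels in Study vigilance.

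**Inputs**

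1. Procedures: induced sputum, gastric aspirate and nasopharyngeal aspirate (Participant flow). Stool is also listed, but it is neither aspirated nor induced and is left out of the comparison. Grouping the other three is a reading of the list; the article does not rank their risks.
2. Routine channel: gastric aspiration in children, nothing else (Study vigilance).
3. Serious channel: death or a life-threatening event, after any procedure (Study vigilance).
4. Definition of a serious event: includes hospitalisation, disability and other medically important events (Study vigilance).

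**Which channel takes which event**

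| Event in a child | After gastric aspiration | After induced sputum | After nasopharyngeal aspiration |
|---|---|---|---|
| Fatal or life-threatening | Serious channel | Serious channel | Serious channel |
| Hospitalisation or other serious event, neither fatal nor life-threatening | Routine channel | Neither | Neither |
| Not serious | Routine channel | Neither | Neither |

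**Reading the table**

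- The first row has no gap.
- The second and third rows are empty for two of the three procedures. No other section of the article adds a channel.
- The second row matters most, because those events meet the protocol's own definition of serious.

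**Does the stated reason account for the difference?** Low risk and the absence of an intervention are properties of the whole study. They can justify light reporting overall. They do not distinguish gastric aspiration from the two procedures listed with it.

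**Does the reference to national guidelines account for it?** No. It governs the whole list, gastric aspiration included, so it cannot be why one item is reportable and the other two are not.

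**The case against.** The strongest reply is that this is a deliberate choice, openly explained. Defining events broadly by a standard and then reporting a subset is common and is not itself a contradiction. Participant flow promises no safety reporting, so in the strict sense the two sections do not conflict. Ethics approvals are listed for the master protocol and for each country, and the article condenses vigilance procedures that are not shown. All of that stands, and the point does not rest on calling the two sections contradictory.

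The condensed format is only a partial answer. The article does not leave the scope of reporting open; it closes it with words of exclusion. If the full procedures do capture these events, the article misstates them and needs correcting.

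It is also fair to say that the article does not state how often each procedure is used. A child may give only stool or only a gastric aspirate, and the article does not say which collections go beyond routine care in either country. That leaves the size of the gap unknown but does not close it.

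Several stronger readings are tempting and are not supported:

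- *A child hospitalised after these procedures would be reported nowhere.* Fatal and life-threatening events are still reported after any procedure. Reporting through routine care is not described and cannot be excluded.
- *Harm from these procedures cannot be detected.* The section limits reporting. It does not limit detection or recording, and its provisions on severity and causality are not confined to gastric aspiration.
- *The trial's safety profile or its comparison of procedures would be biased.* The study endpoints include no safety endpoint, and no comparison of collection procedures is planned.

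**Conclusion.** The point holds in a limited form. On the rules as written, an event after induced sputum or nasopharyngeal aspiration in a child that is neither fatal nor life-threatening enters neither study channel. This includes a procedure-related hospitalisation that the protocol itself calls serious. The reason given for light reporting does not explain why gastric aspiration is treated differently.

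In size, the gap covers two of three listed procedures and two countries, with an unstated number of children and no event rate in the article. It is a weakness of participant safety oversight and has no bearing on the diagnostic accuracy endpoints.

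The conclusion assumes that the article describes the study's reporting rules completely. Its closed wording suggests this, but the full vigilance procedures are not available to confirm it.

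**What to change.** Reconcile the Study vigilance and Participant flow sections with two changes:

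1. Extend the routine adverse event reporting that already exists for gastric aspiration to induced sputum and nasopharyngeal aspiration in children.
2. Add to the serious channel any hospitalisation that the investigator judges related to a study specimen procedure. Causality assessment is already planned, so no new judgement is asked of the investigator. Limiting the rule to related admissions keeps out admissions for the underlying illness, which matters because the sample size section allows inpatients to be recruited to enrich the paediatric group.

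If the narrower scope is intended, state why gastric aspiration alone is reportable. If the full procedures already cover these events, correct the article to say so.

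The cost is a sentence or two of text, existing reporting applied to two more procedures, and a small increase in reporting workload in Cameroon and Viet Nam. Design, sample size and analysis stay as they are.

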### Ethical statement

Ethics approval has been granted for Phase 1 only (WHO ethical review committee approval ERC.0003921). Oversight is provided by country ethical research committees (ERCs), the Liverpool School of Tropical Medicine (LSTM), and Stop TB Partnership, shown in Table 2. The potential risks and benefits to participants are outlined in the patient information leaflet (Supplementary Material 3). Quality assurance is overseen by LSTM with all countries providing source data where possible from all assays.

**Table 2. tbl2:** Master and country ethical research committees’ identification codes.

Body	Number
LSTM REC	22-084
WHO ERC (master protocol)	ERC.0003921
WHO ERC Bangladesh	ERC.0004062
WHO ERC Brazil	ERC.0004061
WHO ERC Cameroon	ERC.0004014
WHO ERC Kenya	ERC.0004079
WHO ERC Malawi	ERC.0004033
WHO ERC Nigeria	ERC.0004062
WHO ERC Viet Nam	ERC.0004084

LSTM = Liverpool School of Tropical Medicine; WHO = World Health Organization; REC = research ethics committee; ERC = ethical research committee.

## CONCLUSIONS

By assessing combinations of WHO-endorsed and experimental screening tools, Phase 1 of Start4All will provide evidence to inform how these innovations can be integrated into practice to improve diagnostic access and efficiency. Start4All’s focus on algorithmic testing reflects a shift from single-test evaluation toward an integrated diagnostic ecosystem, consistent with WHO’s call for evidence-based test combinations that balance accuracy, affordability, and feasibility across levels of care.^22^ A defining feature of Start4All is its implementation within NTPs across seven high-burden countries. This approach ensures that findings are directly translatable to policy and operational decision making. Harmonised protocols, standardised microbiological reference testing, and unified data management systems will enable cross-country comparison and strengthen the external validity of results. Importantly, by embedding the study in routine service delivery environments, rather than controlled research settings, Start4All captures real-world operational challenges and enablers, providing policy-relevant insights into how diagnostic innovations can be sustainably scaled.

The inclusion of children, PLHIV, and other target populations reflects the TB community’s priority to address inequities in TB detection.^23^ Evaluating both sputum and non-sputum-based tests acknowledges the diagnostic limitations of sputum-dependent algorithms in these populations. The inclusion of CAD interpreted CXRs is particularly relevant for countries seeking to decentralise radiographic screening to lower care levels and community settings where radiologists are scarce and CXR interpretation quality is likely a challenge. These insights will inform global and national guidance on the role of digital health tools, non-sputum diagnostics, and optimised laboratory processing (Xpert Ultra pooling) in expanding equitable access to TB screening and diagnosis. Start4All will also contribute to the global evidence base on diagnostic pathways and cost-effectiveness. The inclusion of acceptability, feasibility, and implementation assessments ensures that recommendations extend beyond technical accuracy to include considerations of user experience, workflow integration, and health system readiness, all critical determinants for policy adoption.

Conducting this evaluation across diverse epidemiological and programmatic contexts presents challenges. Variations in HIV prevalence, health care infrastructure, and workforce capacity may influence diagnostic performance and operational feasibility. Start4All mitigates these limitations through rigorous quality assurance procedures, structured training, and cross-country coordination, ensuring consistency in implementation. While experimental test results are not used for clinical management in Phase 1, this design safeguards methodological integrity and provides the evidence foundation for future work. Start4All supports the broader goal of accelerating progress toward universal access to TB diagnosis and care, and ending TB as a public health threat by 2035. It is anticipated that the outcomes from this study will provide policymakers, implementers, and global health partners with a robust evidence base to guide the rational integration of novel diagnostic technologies into TB screening and diagnostic algorithms.
